**Inclusion Criteria**:
1. Men and women aged 19–70 years
2. Patients who experience intermittent pain persisting for more than three months in either or both temporomandibular joints (TMJ) according to the Diagnostic Criteria for Temporomandibular Disorders (DC/TMD)
3. Patients whose average pain intensity in the most painful TMJ (for bilateral pain, the more painful side was considered) over the past week is ≥ 40 mm on the Visual Analogue Scale (VAS)
4. Patients who present with localized pain in the TMJ or surrounding areas (temple, ear canal, or preauricular area) induced by jaw movement, function, or parafunction
5. Patients whose pain is confirmed by palpation of the temporalis muscle, masseter muscle, or the lateral pole of the mandibular condyle, corresponding to myalgia, myofascial pain, or arthralgia, or those with a headache located in the temporal region that is provoked or aggravated by jaw movement and is reproducible upon examination

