### Safety assessment

For safety assessment, the occurrence of adverse events (AEs) and their potential relationship with the intervention (TBT or TENS in the control group) will be evaluated. The safety of the intervention methods will also be assessed through the measurement of vital signs and participant interviews regarding any discomfort or safety concerns experienced following the intervention. Both vital signs and AEs will be monitored and assessed at each visit from weeks 1 to 6, as well as at the follow-up visit in week 10.

The criteria and methods for safety evaluation include the documentation of all AEs and vital signs. Safety assessments will be conducted for all participants enrolled in the study (the intention-to-treat (ITT) population). Any undesirable medical findings or symptoms not observed before the start of the clinical trial will be classified as AEs.

In preparation for any adverse symptoms that may arise during the study period, appropriate medical actions will be taken if any new symptoms, not observed before the initiation of the clinical trial, occur. The investigators will record the date of onset, severity, outcome of the AE, actions taken regarding the intervention, the causal relationship between the AE and the intervention, any other suspected medications, and treatments provided for the AE. The principal investigator will ensure continuous follow-up until the AE resolves or the participant’s condition stabilizes.

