#### Safety analysis

AEs will be recorded at each visit through spontaneous reporting and systematic questioning. The incidence, severity, and causality (relatedness to intervention) of AEs will be summarized using descriptive statistics and compared between groups using Fisher’s exact test or chi-square test.

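### The adverse-event definition covers new findings but not worsening, so a flare of the TMJ pain every participant has at entry would not count as an AE

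*Protocol article*

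**What the plan says.** The Safety assessment section states the classification rule: "Any undesirable medical findings or symptoms not observed before the start of the clinical trial will be classified as AEs". The paragraph after it uses the same test of prior absence for a different purpose, providing for medical action "if any new symptoms, not observed before the initiation of the clinical trial, occur". The article gives no other AE definition, and neither this section nor Safety analysis refers to a change in severity, frequency or duration of a symptom that was already there.

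Two collection routes are described. Safety assessment includes "participant interviews regarding any discomfort or safety concerns experienced following the intervention", and Safety analysis says that "AEs will be recorded at each visit through spontaneous reporting and systematic questioning". The formal comparison, however, is of AEs: "The incidence, severity, and causality (relatedness to intervention) of AEs will be summarized using descriptive statistics and compared between groups".

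In Table 1, inclusion criteria 2 to 4 require TMJ pain for more than three months, a past-week average of at least 40 mm, and pain induced by jaw movement, function or parafunction. Temporal headache appears only as an alternative within criterion 5. Limited opening is not an entry criterion, although the Background names restricted jaw movement as a common feature of the disorder.

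**The concern.** The definition turns on whether the symptom was there before the trial. In a trial of a chronic pain condition, the index symptom was there by design. Both arms act on the painful region: TBT holds the jaw in position with an appliance and adds myofascial release and jaw stretching, and TENS stimulates over the masseter. The TENS section itself recognises that stimulation can provoke pain, because the intensity is to be set to avoid it. Exacerbation of local pain is therefore a plausible harm on the article's own account.

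Safety is a stated aim in the Background, in Study design and in the Discussion. If exacerbations are not classified as AEs, the AE comparison cannot show a difference between arms in how often treatment provokes them. Two investigators facing the same flare could also classify it differently, one following the wording and the other following ordinary practice. The Blinding section says that treating investigators know the allocation, and the article does not say who classifies AEs, so such discretion could differ by arm.

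**Working it through.** There is no plan figure to reproduce. The check sets the AE rule beside the entry criteria, the collection routes and the outcome schedule.

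**1. Which symptoms were observed before the trial, and in whom?**

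| Symptom | Status at entry (Table 1) | Worsening of it an AE as written? | New onset an AE as written? |
|---|---|---|---|
| TMJ pain | Required of all (criteria 2–4) | No, for all 30 participants | Does not arise for the index pain |
| Temporal headache | Alternative route in criterion 5 | No, in those who have it at entry | Yes, in those who do not |
| Limited opening | Not an entry criterion | No, in those who have it at entry | Yes, in those who do not |

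The gap is universal for TMJ pain. For the other two symptoms it is confined to a subset whose size the article does not give.

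**2. Do the collection routes close the gap?** The discomfort interviews and the systematic questioning are not limited to new symptoms, so the information may well be gathered. They are ways of asking, however, and do not alter what is classified. Only AEs enter the comparison in Safety analysis, and the record of onset, severity, outcome, causal relationship and action taken is prescribed only for AEs.

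**3. Do the efficacy outcomes close the gap?**
- Average pain VAS is read at weeks 0 and 6 for the primary outcome, and at weeks 0, 6 and 10 for the secondary analysis. Its recall period is the past week.
- Opening and JFLS-8 are taken at baseline, week 6 and week 10, and PGIC at weeks 6 and 10.
- Treatment runs for 6 weeks with 2 sessions a week. If the week 6 reading is taken at the end of treatment (an assumption about timing), its one-week recall covers 1 of 6 treatment weeks. The other 5 weeks, with 5 × 2 = 10 of the 12 sessions, fall outside it.
- Worst-pain VAS could reach further back, but the article does not give its recall period.

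So a worsening that lasts to week 6 or week 10 would be seen. A flare after an early session that has settled by week 6 could leave no trace in average pain or opening. None of these measures carries a judgement of relatedness.

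**4. Size.** If r is the proportion of an arm with a treatment-provoked exacerbation, 15 × r participants per arm go uncounted for that event. The article gives no r, so no number follows. Each such participant is 1/15 = 6.7 percentage points of arm-level incidence.

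The effect on the test is smaller than the effect on the description. With Fisher's exact test (two-sided), 0/15 against 4/15 gives p = 2 × 1365/27405 = 0.0996, and 0/15 against 5/15 gives p = 2 × 3003/142506 = 0.042. Against zero events in the other arm, adding one or two would not make the comparison significant, but it would change the reported incidence.

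**The case against.** The strongest reply has four parts.

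- **The sentence does not say that only new findings count.** That is true as a matter of wording. But no wider rule appears anywhere in the article, and the next paragraph repeats the new-symptom test, so the narrow reading is the natural one.
- **The article condenses a fuller protocol.** Data Availability says that the approved protocol is a supplement, which is not shown here and may define AEs more broadly. This limits what can be said about trial conduct. It does not rescue the article, which states a definition rather than leaving one out; if the supplement is broader, the article misreports it.
- **Deterioration is measured elsewhere.** Pain VAS, opening, JFLS-8 and PGIC are all compared between arms, and PGIC has an end for becoming very much worse. This stands for sustained worsening. It does not stand for transient flares or for causality.
- **A broad rule would flood the AE table.** Criterion 2 describes the pain as intermittent. Counting any increase at any visit would turn ordinary fluctuation into AEs and duplicate the primary outcome. This stands, and the fix must contain a threshold.

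A reader might also infer more than the article supports. One inference is that worsening of jaw pain, headache or opening can never be an AE; new headache or newly limited opening does qualify, and only TMJ pain is universal at entry. Another is that these are the most likely harms; the article lists no expected harms and no rates. A third is that the AE table would look clean even if an arm made patients worse overall; the primary outcome would show that. A fourth is to size the defect by the upper bound on a zero count, 1 − 0.05^(1/15) = 18.1% (one-sided 95%). That figure is a property of 15 per arm under any AE definition and says nothing about this one.

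**Conclusion.** The point holds in a limited form. As stated in the article, the AE definition omits worsening of pre-existing symptoms. For TMJ pain this affects all 30 participants; for headache and limited opening it affects only those who have them at entry. Treatment-provoked exacerbations would be left out of the between-group AE comparison, and transient ones may also escape the efficacy outcomes.

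The conclusion rests on reading the definition literally and on no broader rule applying in the supplement. The number of events lost is unknown. The primary efficacy analysis is not affected. The point is worth correcting because safety is a stated aim and the change is small.

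**What to change.** Define an AE as any undesirable finding or symptom, whether or not judged related to treatment, that is either new or shows clinically relevant worsening from baseline. State in advance the threshold for worsening, beyond the participant's usual fluctuation and with the baseline record as reference. The article gives no basis for a particular value, so the trial team should set and justify one. Add a line to the AE form for worsening of a pre-existing symptom, and report that line separately by arm so that new events and exacerbations can be told apart.

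The sentence on medical action, "appropriate medical actions will be taken if any new symptoms, not observed before the initiation of the clinical trial, occur", uses the same wording and should be checked for consistency with the revised definition. What action follows is for the trial team to decide.

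The Trial status section gives recruitment from 11 February 2025 to about 30 June 2025. If recruitment has ended, apply the definition to the existing visit and interview records, preferably by someone unaware of allocation, and label the result as a reclassification. How complete it is will depend on how much detail those records hold. If the supplement already includes worsening, it is enough to amend the article to match.

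The cost is one sentence, one form line, some more AE records and partial overlap with the pain outcome.

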### Cost-effectiveness evaluation

A cost-effectiveness evaluation will be conducted based on the cost and outcome data collected during this study to compare the cost-effectiveness between the intervention group and the control group. The primary analysis period is set at 10 weeks (corresponding to the study’s follow-up duration). If projection beyond these 10 weeks is required, long-term modeling such as a Markov model will be used. When the total analysis period (time horizon) exceeds 12 months, all costs will be standardized to 2024 Korean Won (KRW), and a 4.5% annual discount rate will be applied, based on the HIRA economic evaluation guidelines.

Effectiveness will be estimated using Quality-Adjusted Life Years (QALYs) and individual clinical outcome indicators measured according to the clinical trial schedule after randomization. QALYs will be measured using the validated Korean version of EQ-5D-5 L and calculated using the Korean-specific tariff developed by Kim et al. (2016) [27]. Individual effectiveness indicators will be derived from the primary and secondary clinical outcome measures as defined in the trial protocol.

Cost estimation will be performed using a micro-costing approach that multiplies the unit cost by usage volume for each cost item. Institutional data on resources and time required for TBT and TENS procedures will be collected internally. Participant-level cost data will be collected through surveys administered at Week 0, Week 6, and Week 10, capturing costs incurred over the preceding six weeks. Productivity losses will be assessed using the WPAI: GH 2.0 instrument, which evaluates productivity loss over the previous seven days. These results will be extrapolated using interpolation to estimate productivity losses over six weeks.

The analysis will be conducted from both the healthcare system perspective (including direct medical costs) and the societal perspective (including direct medical costs, non-medical costs, and productivity losses). Because the primary analysis period is less than one year, discounting will not be applied.

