## Methods/design

### Study design

This study will be a single-center, randomized, assessor-blinded, active-controlled, parallel-group clinical trial designed to evaluate the efficacy, safety, and cost-effectiveness of TBT for TMD. A total of 30 participants will be recruited and randomly assigned in a 1:1 ratio to the TBT experimental group and TENS control group. The study consists of a screening visit, 12 treatment visits over 6 weeks (twice weekly), and a follow-up visit at week 10. The detailed study design is summarized in Fig. 1; Table 1. This protocol adheres to the Standard Protocol Items: Recommendations for Interventional Trials (SPIRIT) 2013 guidelines and checklist (Supplementary material 1) [24]. The flowchart of this study is shown in Fig. 1. The SPIRIT schedule of enrollment, interventions, and assessments is shown in Fig. 2.

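### The six-week recall at Week 10 and the six-week productivity period do not fit the 10-week economic horizon

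*Protocol article*

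**What the plan says.** All the relevant statements are in the protocol article.

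- **Horizon** (Cost-effectiveness evaluation): "The primary analysis period is set at 10 weeks", which the article ties to the length of follow-up.
- **Visit spacing** (Study design): "12 treatment visits over 6 weeks (twice weekly), and a follow-up visit at week 10".
- **Participant-level costs** (Cost-effectiveness evaluation): "surveys administered at Week 0, Week 6, and Week 10, capturing costs incurred over the preceding six weeks". One recall length serves all three surveys.
- **Productivity** (same section): the WPAI is the instrument, "which evaluates productivity loss over the previous seven days". Then: "These results will be extrapolated using interpolation to estimate productivity losses over six weeks".
- **Use** (same section): productivity loss enters "the societal perspective (including direct medical costs, non-medical costs, and productivity losses". The healthcare system perspective takes direct medical costs only.
- **Procedure costs** (same section): resources and time for TBT and TENS are collected by the institution, not from participants.

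The Cost-effectiveness analysis section gives the ICUR and ICER as differences in total cost over differences in effect, and refers to imputation of missing data. Neither section gives a shorter recall at Week 10, a rule for combining the surveys, or an extension of productivity loss to 10 weeks.

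**The concern.** Costs and effects in an ICER or ICUR should cover the same period. Here the article states the period and also the windows over which cost data are gathered, and the two do not agree. A six-week recall suits the Week-6 survey, because six weeks have passed since baseline. At Week 10 only four weeks have passed since the last survey, so the recall reaches back into the final two treatment weeks. At two visits a week, those weeks hold 4 of the 12 sessions. The productivity sentence also names six weeks, and no reading of it yields 10.

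What is at stake is the survey-based part of the cost numerator in both perspectives, and the productivity part in the societal perspective. Cost-effectiveness is a named aim of the trial. The Background expects TBT effects to last, so a productivity figure ending at Week 6 would miss the weeks in which a lasting benefit would show.

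**Working it through.** **Inputs.** Horizon 10 weeks; surveys at Weeks 0, 6 and 10; recall 6 weeks; productivity scaled to 6 weeks (all from Cost-effectiveness evaluation). Treatment lasts 6 weeks with follow-up at Week 10 (Study design).

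**Step 1: the plan's own figure.** Six treatment weeks plus four follow-up weeks = 10 weeks. The stated horizon reproduces.

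**Step 2: recall windows.** A survey at week t with a six-week recall covers t - 6 to t.

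| Survey | Window (weeks) | Weeks inside the horizon |
|---|---|---|
| Week 0 | -6 to 0 | 0 |
| Week 6 | 0 to 6 | 6 |
| Week 10 | 4 to 10 | 6 |

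The two post-baseline windows together cover all 10 weeks, but their lengths add to 6 + 6 = 12. The overlap is 12 - 10 = 2 weeks (weeks 4-6). The Week-0 window lies wholly before the horizon.

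**Step 3: size if the two surveys are simply added.** Let weekly survey-reported cost be r in weeks 0-6 and 1 in weeks 6-10. The true total is 6r + 4, and the summed total is 6r + (2r + 4) = 8r + 4. The overstatement is 2r / (6r + 4). The article gives no cost rates, so r is an assumption:

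| r | True | Summed | Overstatement |
|---|---|---|---|
| 0.5 | 7 | 8 | 14% |
| 1 | 10 | 12 | 20% |
| 2 | 16 | 20 | 25% |
| 3 | 22 | 28 | 27% |

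These percentages describe one arm's survey-reported total, not the incremental cost.

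**Step 4: the incremental numerator.** Let D be the mean weekly between-arm difference in survey-reported cost during weeks 4-6. Simple addition shifts the incremental cost by 2 x D. If D = 0 the error cancels. If not, the relative error can be small or large. As an assumed illustration, take a difference of +1 unit per week on treatment and -1 unit per week afterwards. The true difference is 6 - 4 = 2, and the summed surveys give 6 + (2 - 4) = 4. The article gives nothing from which D could be estimated.

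**Step 5: productivity.**

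- Read as six weeks in total: 6/10 = 60% of the horizon is covered and 4/10 = 40% is left out.
- Read as six weeks per survey: the Week-6 and Week-10 estimates cover 0-6 and 4-10, again 12 weeks with a two-week overlap.

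Neither reading gives 10.

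**Step 6: after correction.** If Week-10 costs start at the Week-6 visit, 6 + 4 = 10 weeks, with no gap or overlap.

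**The case against.** The strongest reply is that the article describes how data are captured, not how they are combined. Nowhere does it say that the Week-6 and Week-10 surveys will be added. Recalled costs could be turned into weekly rates or trimmed to the horizon, and the full protocol, cited as a supplementary file, may say so. This stands in part. The overlap is stated; double counting is only its consequence if nothing is done. But the objection does not remove the conflict, because the article prints specific windows that disagree with its own printed horizon. Recall length is also fixed when the data are collected. Without item dates, no later analysis rule can separate weeks 4-6 exactly, and the planned one-way and probabilistic sensitivity analyses do not remove a systematic overlap.

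A reader might further infer that the error cannot cancel between arms because the repeated weeks fall on treatment. The article does not support this. Both arms have 12 sessions on the same twice-weekly schedule at one centre, so travel to trial visits should be about equal and would largely cancel. Nothing shows that other survey-reported costs differ most between arms in weeks 4-6.

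A reader might also infer that 40% of the productivity period is certainly lost. That holds on one reading only. The productivity sentence follows closely on the per-survey recall, so six weeks per survey is a plausible meaning, and on that meaning nothing is left out.

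**Conclusion.** The point holds as an internal inconsistency. The recall windows total 12 weeks against a 10-week horizon, with weeks 4-6 in both, and the productivity period fits the horizon on neither reading. This follows from the text alone.

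The consequences are conditional. The 20% figure assumes that the surveys are summed as collected and that weekly cost is even; the assumed cost patterns tried above give 14% to 27%. A reader might take 20% as the bias in the ICER or ICUR, or conclude that both numerators are wrong throughout. The documents support neither: the figure concerns one arm's survey-reported total, procedure costs come from institutional data, and the incremental effect cannot be estimated.

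The problem is confined to the economic evaluation. It should be settled before the cost data are analysed, but it does not touch the primary VAS comparison or the sample size.

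**What to change.** 1. **Week-10 survey costs.** Count them only from the Week-6 visit onward. Where forms can still be changed, set the Week-10 recall to the time since the Week-6 visit. Otherwise use item dates. If there are none, pre-specify how the six-week recall is apportioned between weeks 4-6 and 6-10, with a sensitivity analysis on that split.
2. **Week-0 survey costs.** State that they are a pre-randomisation baseline and stay outside the 10-week total.
3. **Productivity loss.** Estimate it over the full 10 weeks. One option is to interpolate the weekly WPAI values: (w0 + w6)/2 x 6 + (w6 + w10)/2 x 4. This assumes that the WPAI is completed at the same three visits as the cost surveys. Reword the sentence on the six-week period accordingly.

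The form change is one line but may come too late. Recruitment began on 11 February 2025 and was due to end on 30 June 2025, so on that plan the last Week-10 visit falls around early September 2025. After that, the remaining cost is a short analysis rule, fixed before the cost data are examined, plus one sensitivity analysis. Apportionment reduces the problem but cannot recover the timing that undated items lack.

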### Assignment of interventions

#### Allocation

The randomization process will be managed by a statistician who is not involved in the conduct or assessment of the clinical trial. The randomization officer will generate the randomization list using a specifically planned and reproducible method, employing Python 3.12.4 (Python Software Foundation, Wilmington, DE, USA) to ensure equal probability of assignment for each participant. Block randomization will be used to maintain balance between groups, with participants allocated to the intervention (TBT) and control (TENS) groups in a 1:1 ratio.

The randomization list will be sealed and stored in a manner that allows confirmation of whether the seal has been broken, and will be managed separately by the principal investigator. For allocation, the study coordinator will open the randomization envelopes sequentially in front of the participant at the time of assignment. Each opened envelope will have the date of opening and the study coordinator’s signature recorded and will be stored separately for documentation.

Participants who provide written informed consent and undergo screening will be assigned a screening number in the format DJ-S-001 (where DJ refers to Daejeon University Daejeon Korean Medicine Hospital, S indicates Screening, and 001 is the serial number). Only those who meet the inclusion and exclusion criteria after the eligibility assessment will be assigned a subject identification code in the format DJ-E-001 (where E indicates Enrollment).

